### Measures

As noted, outcome measures will be collected at 5 assessment points: Pre, Mid, Post, 3 m and 6 m FU. Given the time-intensive nature of the diagnostic interviews for participants, they will be collected at Pre, Post, and 6 m FU only. ACT process measures will be administered at Sessions 2, 4, and 6 of the intervention. Self-reported outcomes will be programmed and administered online in Qualtrics to ensure accurate data collection (or post mail if a participant lacks internet access). To encourage completion of the outcome measures, participants will be paid $25 per assessment point for measure completion, $25 per diagnostic interview completed, and $50 for a completed medical tracker (see Medical Utilization). Starting mid-way through the study, to encourage more timely measure completion, we began paying participants a $10 bonus for completing the questionnaires within 36 h of their receipt. Participants who drop out of the study will be given the opportunity to complete the study assessments. Diagnostic interviews will be conducted by phone with well-trained assessors who are blind to condition assignment (see Anxiety Disorders/ Diagnostic Interview). Cancer type and stage will be verified whenever possible through medical chart review.

#### Screening measure

The screener aims to identify cancer survivors who are notably anxious about cancer and anxious or depressed in their daily lives. Thus, anxious cancer survivors are eligible even if they also endorse depressive symptoms, reflecting the finding that anxiety and depressive symptoms frequently co-occur among cancer survivors [68] and more generally [69]. The 11 screening items include: 1) a validated 6-item version of the *State-Trait Anxiety Inventory* (STAI; [70]) that inquires about anxiety over the past month. The STAI is the most commonly used measure to identify which cancer patients benefit most from psychosocial interventions [35]. 2) The 4-item *Patient Health Questionnaire* (PHQ-4; [71]) brief measures of anxiety and depression symptoms, selected for brevity, ease of scoring, and consistency with the most recent American Society of Clinical Oncology distress screening guidelines [72]. 3) A 0–10 rating of “your current anxiety about cancer or the effects of cancer treatment”. Based on the Valued Living pilot study [59] and published validation studies, we will use the following as the cutoff for study eligibility: (1) a 5+ on the “anxiety about cancer” scale, which indicates moderate to severe anxiety about cancer *and* (2) a score of 14+ on the brief STAI [73] *or* 3+ on either the anxiety or depression scale of the PHQ-4 [71], which indicates significant anxiety or depressive symptoms in daily life.

### Primary outcome

#### Anxiety symptoms

The validated, widely-used *Hospital Anxiety and Depression Scale* (HADS; [74]) anxiety subscale will serve as the primary outcome due to its focus on broad anxiety symptoms and its wide use to evaluate anxiety and distress among cancer patients and survivors (e.g., [75, 76]).

### Secondary outcomes

#### Fear of recurrence

The *Concerns about Recurrence Scale* (CARS; [77]) will assess fear of cancer recurrence, which we adapted for all cancer types by substituting “cancer” for any reference to a specific form of cancer (i.e., “breast cancer”). Per our pilot study [59], we will specifically use the 4-item overall fear of recurrence subscale (e.g., “How much time do you spend thinking about the possibility that your cancer could recur?”, “How afraid are you that your cancer may recur?”).

#### Depressive symptoms

The 20-item *Center for Epidemiologic Studies Depression Scale* [78] will be used to assess depressive symptoms. The CESD was developed for use in medical populations [79] and is widely used and validated within cancer populations [78, 80].

#### Cancer-related trauma symptoms

The *Revised Impact of Events Scale* [81] will assess cancer-related hyperarousal, behavioral avoidance, and intrusion-related symptoms, which are known to be elevated among cancer patients and survivors [82].

#### Vitality/fatigue

The widely-used 4-item *SF-36 Vitality Scale* [83] assesses vitality/fatigue levels. This measure has been validated as a measure of energy/fatigue levels in cancer populations [84].

#### Sense of life meaning

The *Functional Assessment of Chronic Illness Therapy Spiritual Well-Being Scale,* meaning/peace subscale [85] will assess sense of life meaning. This validated measure has been widely employed in studies with cancer patients and survivors (e.g., [86, 87]) to assess a sense of meaning and purpose that is not specific to any particular religious or spiritual orientation.

#### Anxiety disorders/ diagnostic interview

At Pre-, Post- and 6-month FU, we will assess the presence and severity of anxiety disorders using the Mini-International Neuropsychiatric Interview (MINI) for DSM-5 [88]. The MINI will be enhanced with detailed diagnostic questions for anxiety disorders used in previous anxiety disorder studies and a more detailed suicidality assessment (e.g., [89]). As a diagnostic interview approach, the MINI possesses good test-retest reliability (70% of kappas are above 90%) and adequate concordance with other widely-used diagnostic instruments such as the Structured Clinical Interview Diagnostic and the Composite International Diagnostic Interview [90]. Disorder severity will be assessed with the validated 0 to 8 clinical severity rating (CSR) scale for each DSM disorder detected at the clinical or sub-clinical level [91].

Professional research assistants and clinical psychology doctoral students will conduct the MINI interviews after 10 to 15 h of training, including co-rating three gold standard training interviews from an independent research group, and demonstrating diagnostic and CSR accuracy on two to three gold-standard, recorded interviews from our own laboratory, and being coached in real-time by an experienced interviewer for their first two live patient interviews. Diagnoses and CSR ratings will be reviewed in weekly supervision with a licensed clinical psychologist ([name]). As noted above, interviewers and [name] will be blind to study condition.

#### Medical utilization

The *Medical Tracker*, based on previous psycho-oncology studies that have tracked medical utilization [39, 92], has participants track their medical appointments as well as appointments related to mental health and well-being such as support group(s), counseling, and related resources. It tracks the date of the appointment, the reason for the visit, including whether this visit was “related to your experience with cancer?”, the type of provider, whether the visit was a routine/ regular appointment or for a problem, whether they attended the appointment, and if so, how many minutes the appointment lasted. The medical tracker has two purposes: 1) to track attendance at routine cancer-related appointments and initiation of problem-related oncology visits, which serve as secondary outcomes, and 2) to track use of non-study supportive care and mental health care to account for their use in the statistical analyses. A randomly selected 15 to 20% of RMCC patients enrolled in the study will be selected for medical chart review to confirm the information listed by the patient in the *Medical Tracker*. Please note that for ethical reasons, participants will be permitted to pursue psychosocial interventions and support outside of the study; however, we will request that they track this care in their Medical Trackers.

### Process measures

We will use two measures to assess two core therapeutic processes hypothesized in ACT: experiential avoidance (the reverse of openness and acceptance of internal experience) and values-driven behavioral change [57] The *Brief Experiential Avoidance Questionnaire* [93], based on the longer *Multidimensional Experiential Avoidance Questionnaire* (MEAQ; [94]), is a psychometrically robust measure of experiential avoidance, the tendency to avoid challenging internal experiences such as negative thoughts and feelings. The BEAQ holds very similar psychometric properties as the MEAQ, which is distinct from neuroticism and negative affect [95].

The Bull’s Eye Values Survey part 1 [96] is a validated measure of values-driven behavior that is sensitive to ACT treatment effects. The original Bull’s Eye part 1 visually assessed the degree to which participants perceive living in accordance with their personal values in 4 domains: health, relationships, work/education, and leisure. Based on pilot participant and provider feedback, we adapted these for the current study to represent the following 5 domains: health & self-care, family relationships, social relationships & community, work/education, and leisure. We will administer the Bull’s Eye and BEAQ process measures at the beginning of group sessions 2, 4, and 6 using participant ID numbers rather than personal identifiers, and sealed envelopes to protect confidentiality, as well as during the full assessments in Qualtrics at baseline, post, 3- and 6-month FU.

### Power and sample size estimation

To estimate power for the hypothesized effects and to allow for the possibility of missing data in that estimation, we took a multi-faceted approach involving both existing software for power calculation in longitudinal multilevel linear modeling (PINT; [97, 98]) as well as a cutting-edge simulation approach (see [99, 100]). We started with hypothesized means on the main outcome (anxiety) for the treatment group and controls at each of four time points (baseline, post, 3- and 6-month FU). For the treatment group, these hypothesized means come from our pilot data [59]; the UC control group means represent a conservative expectation based on existing data from published studies [101]. Both sets of means show declines (linear and quadratic) over time, with weaker time effects for the control participants. Model specification involved a multilievel linear mixed model, specifying linear and quadratic effects of time (differing by condition), with random intercepts and time slopes for participants within groups. Power was estimated both for mean condition differences at each point in time as well as the condition by linear time interaction. Given the conservative means and the variance components, the hypothesized effect sizes were medium (*d* ~ .50) [102].

With no missing data and sample sizes of *n* = 50 in each group, the power to detect a significant condition by linear time interaction was 90% or greater. The power to detect the mean difference at 3-month FU was 88%. Simulations and PINT power software produced the same results, confirming excellent levels of power.

We then allowed data to be missing at random as a function of time (20% missing at Post; and 25% missing at each 3- and 6-month FU) – a situation that simulations can model [99, 100]. Our estimation that at least 75% of the sample will complete the 6-month FU (i.e., assuming 25% missing data at the final assessment point) is conservative. Even with this level of missing data, the power to detect a significant mean group difference at each Post and FU remained 81% or greater.

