## Methods/Design

### Study design

This two-armed, prospective randomized controlled trial (RCT) will randomize a minimum of 100 anxious re-entry-phase cancer survivors to group ACT (the Valued Living intervention) or a UC control condition. Participants will be randomized on a 1:1 ratio to ACT or UC using a computer-generated block randomization sequence done by a consulting biostatistician who is otherwise uninvolved in the study. All participants will be assessed at 5 points: baseline (Pre), mid-intervention (Mid), post-intervention (Post), and 3- and 6-month follow-up (3 m and 6 m FU). The Post assessment will occur 1 week after the final group session and the 3 m and 6 m FU will occur 3 and 6 months after Post. In addition, ACT participants will complete process measures before the beginning of group sessions 2, 4, and 6; all participants will complete the process measures during the regular assessments as well.

We considered alternative study designs such as comparing Valued Living to a more active condition, including an alternative psychosocial intervention or single educational session. However, in that this study reflects the first randomized trial of Valued Living, comparison to a staff-demanding condition or one that had not yet been empirically evaluated in the community oncology setting of the study, appeared premature.

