#### Usual care control

Usual Care (UC) will consist of mailing each patient a list of oncology support group resources specifically tailored to each geographic area of recruitment. UC participants will also be encouraged to contact their RMCC social worker (or if they are not RMCC patients, the social worker at their cancer care center) for individual support as needed. UC is designed to provide ethical care for anxious cancer survivors using standard social worker time and resources. In both conditions, we will ask participants to report use of outside supportive and mental health resources on their medical trackers (see below) to account for their use in the analyses.

After the 6-month follow-up (i.e., the final assessment point), UC control participants will be offered the opportunity to participate in an ACT group (free of charge), thus maximizing potential study benefits for all patients. The data from these additional groups will not be included in the primary analyses because we risk confounding the data by comparing cancer survivors at different time points from re-entry and screening, and because we expect that not all UC participants will elect to complete the ACT group. By offering ACT to UC control participants as a benefit of follow-up completion, we aim to enhance patient care without confounding the data.

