#### Valued living intervention

The ACT group intervention known as “Valued Living” will consist of 7 weekly group sessions of 2 h each. The Valued Living groups will meet at participating RMCC offices in group rooms appropriate for this purpose. In addition, participants randomized to Valued Living will be mailed the same list of geographically-tailored oncology support group resources that are mailed to participants randomized to usual care.

The Valued Living intervention is based on a facilitator manual and accompanying participant workbook developed during our single-arm pilot study [59]. In the pilot study, we developed and refined a flexible Valued Living manual based on a multi-step process of soliciting feedback from participants, social work group facilitators, and outside ACT experts. In response to their collective feedback, we iteratively refined the manual, including the overall intervention length, session length, and content.

During the first few group sessions of Valued Living, we introduce and use the Matrix [64], a simple tool to teach core ACT skills including increasing awareness of the link between internal experience and external behavior, personal values and their expression in daily life, and various forms of avoidance and their workability in the short- and long-term. In completing the Matrix, we ask group members to discuss their challenging thoughts and feelings related to cancer and the actions they take to get rid of or escape those feelings (struggle actions). We next have them share who and what are most important to them (values) and what they do when they feel connected to their values (valued actions). Whenever challenging cancer-related thoughts and feelings arise, we have them track their responses, and specifically what they do that moves them towards versus away from their values (or a mix of both).

In the middle Valued Living sessions, participants learn how to respond skillfully to cancer-related concerns and feelings and move towards valued actions, rather than remain stuck in struggle actions. A central tool in these sessions is the Passengers on the Bus metaphor [55], which invites participants to identify persistently challenging thoughts and images about cancer, labeled ‘passengers’. We physically enact this metaphor in the group. In doing so, we practice how to actively accept, and flexibly and compassionately relate to passengers while reducing their dominance over participants’ lives.

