To implement the computer-generated block randomization sequence (see Study Design), the unblinded study coordinator will assign participant ID numbers in the consecutive order in which participants consent, and then link the list of ID numbers for each cohort to a spreadsheet column next to a hidden column of the block randomization sequence. The unblinded study coordinator then will unhide the sequence to determine which participant IDs are allocated to each condition in the ID sequence. The unblended coordinator will communicate condition assignment to participants and will videotape the group sessions and schedule the groups with the onsite social workers. Research team members experienced in ACT, none of whom run the Valued Living groups, will rate 2 randomly selected videos per group (~ 30% of sessions) for fidelity to the manual. They will rate only after extensive training to achieve respectable inter-rater reliability.

The PI can become unblinded to a participant’s study condition by the unblinded study coordinator in order to assess for potential clinical deterioration or emergency, such as in the case of patient-reported or indicated suicidality (assessed in the diagnostic interview, see Anxiety Disorder measures). Participants also can be withdrawn from the study at the PI’s discretion for reasons such as arriving to a group session inebriated or high, or exhibiting disruptive behaviors in group, e.g., yelling at or shaming other group members. To account for such occasional cases, participants will generally be discussed on the basis of their participant ID numbers for study purposes and will be discussed by first name in cases of potential clinical deterioration or study disruption; thus, if the name of a participant is revealed for purposes of PI assessment, then the PI will still remain blind to the participant’s ID number in the study database.

Study results will be communicated by submission to a peer-reviewed journal for publication and reporting of results in clinicaltrials.gov.

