### Data analytic approach

For Aim 1, we will use multilevel mixed modeling to compare the ACT versus UC control groups on the rate of linear and curvilinear improvement, and at each assessment point, to compare between-group means. We will conduct separate intent-to-treat and intervention completer (“protocol adherent”) analyses. The HADS-Anxiety will serve as the primary outcome, although the other outcomes will be analyzed as well.

For Aim 2, to evaluate the session-by-session measures of active acceptance and values-driven behavior, first, we will assess change slopes over time for each process measure. Then, using time-lagged multilevel models, we will assess the extent to which change in active acceptance predicts subsequent change in values-driven behavior and vice versa, to identify the relationship between these two hypothesized ACT processes over time during the intervention. We will also test whether session-by-session change in each process predicts outcomes at Post and FU. If both putative processes significantly change over time and predict outcomes, then using a multiple mediation framework [103], we will assess which ACT process predicts outcomes more robustly when both processes are compared directly, to evaluate which process primarily drives outcomes.

Each analysis will include the hypothesized predictors as well as potential confounding factors (e.g., use of supportive care external to the study, cancer recurrence, age, gender). We will also conduct exploratory moderator analyses through subgroup analyses and moderation models to identify who most benefitted within each condition.

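### ACT is delivered in therapy groups, but the stated power model names no therapy-group variance; if that level is left out and outcomes correlate within groups, standard errors are too small and the stated power is too high

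*Protocol article*

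**What the plan says.** **Delivery.** Under Valued living intervention, ACT "will consist of 7 weekly group sessions of 2 h each", held at oncology offices and led by social workers. Under Usual care control, UC "will consist of mailing each patient a list of oncology support group resources", plus encouragement to contact a social worker individually. UC has no therapy groups during the trial.

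**Allocation.** Study design: "Participants will be randomized on a 1:1 ratio to ACT or UC". The unit is the individual. Under Study ethics and integrity, the unblinded coordinator will "link the list of ID numbers for each cohort" to a block sequence.

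**Power model.** Power and sample size estimation specifies linear and quadratic time effects that differ by condition, "with random intercepts and time slopes for participants within groups". It reports 88% power for the mean difference at 3 months with 50 per arm and no missing data, and at least 81% at each later assessment with 20% to 25% missing. It states no therapy-group variance, ICC, group size or number of groups.

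**Analysis.** Data analytic approach, Aim 1: "we will use multilevel mixed modeling to compare the ACT versus UC control groups". It lists no levels or random effects. The example covariates are outside supportive care, recurrence, age and gender.

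**The concern.** Members of one ACT group share facilitators, each other's company and 7 × 2 = 14 hours of sessions. Their outcomes may therefore be correlated, whereas UC outcomes have no matching structure. A model with only participant-level random effects accounts for repeated measures on one person but treats different ACT participants as independent. With a positive ICC it understates the variance of the ACT mean. The comparison on HADS-Anxiety would then reject too often, its confidence interval would be too narrow, and the power that supports the sample size would be overstated. The secondary outcomes would be affected in the same way wherever they cluster by group.

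**Working it through.** **1. What does *groups* mean in the power section?** Elsewhere in that section the word means arm: the treatment group, the control group, 50 in each group, the mean group difference. The model sentence also covers both arms, and UC has no therapy groups. The arm reading is therefore the more natural one. Even on the other reading, the intercepts and slopes are described as belonging to participants, and no variance is named for the group itself.

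**2. The stated power.** The 88% and 81% cannot be reproduced, because the means and variance components behind them are not printed. They are taken as given below. Two-sided alpha of 0.05 is assumed, as it is not stated.

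**3. Inputs.**
- From the protocol article: 50 per arm ("will randomize a minimum of 100 anxious re-entry-phase cancer survivors", 1:1), power of 88% and 81%, and 25% missing at follow-up.
- Assumed, because the document gives none: m = 7 members per group (about 7 ACT groups) and ICC from 0 to 0.10.

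**4. Formulas** (one time point, clustering in the ACT arm only, normal quantiles).
- ACT design effect: DE = 1 + (m − 1) × ICC
- True over modelled variance of the arm difference: R = (DE + 1)/2
- Actual type I error: 2 × [1 − Φ(1.96/√R)]
- Power: Φ(δ/√R − 1.96), where δ = 1.96 + 1.175 = 3.135 for 88% and δ = 1.96 + 0.878 = 2.838 for 81%

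**5. No missing data, m = 7, starting from 88%.**

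| ICC | DE | R | 1.96/√R | Type I error | Power |
|---|---|---|---|---|---|
| 0 | 1.00 | 1.00 | 1.960 | 5.0% | 88% |
| 0.01 | 1.06 | 1.03 | 1.931 | 5.3% | 87% |
| 0.05 | 1.30 | 1.15 | 1.828 | 6.8% | 83% |
| 0.10 | 1.60 | 1.30 | 1.719 | 8.6% | 79% |

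**6. With 25% missing.** Observed members per group: 7 × 0.75 = 5.25. Starting from 81%:

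| ICC | DE | R | 1.96/√R | Type I error | Power |
|---|---|---|---|---|---|
| 0.05 | 1.2125 | 1.106 | 1.864 | 6.2% | 77% |
| 0.10 | 1.425 | 1.2125 | 1.780 | 7.5% | 73% |

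**7. Sensitivity to group size, no missing data.** At ICC 0.05 and 0.10, type I error is 6.2% and 7.4% with 5 per group, and 7.7% and 10.4% with 10 per group.

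**8. Simulation** (40,000 trials per scenario, single time point). A t-test that ignored groups rejected a true null in 6.0% (ICC 0.05) and 7.3% (0.10) of trials with 5 per group, and in 7.7% and 10.4% with 10 per group. An analysis of ACT group means with Satterthwaite degrees of freedom stayed between 4.8% and 5.5% over ICC 0 to 0.10. This supports both the formula and the remedy.

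**The case against.** **The omission is inferred.** The model sentence uses *condition* for the arms, so participants nested in therapy groups is a tenable reading of it. Aim 1 lists no levels at all, and a condensed article may leave the random-effects structure to an analysis plan that is not shown. This stands. A reader might infer that both models are shown to lack a therapy-group level, but the document does not establish that. It does print power figures and the model behind them, with no sign of a clustering allowance. An analysis plan could add the level to Aim 1, but that would not change what the printed power assumed.

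**The excess depends on the ICC.** A reader might infer that type I error necessarily exceeds 5%. It does not: at ICC 0 there is no excess, and at 0.01 with 7 per group it is about 0.3 points. The facilitator manual, common training, an experienced co-facilitator and fidelity ratings could all hold between-group variation down. They do not ensure that it is zero. Missing data also shrink the observed groups and so the inflation, as step 6 shows.

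**The calculation is for one time point.** It does not quantify the effect on the condition-by-time interaction, which is also powered. This stands.

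**Two further inferences fail.** First, a plain two-sample comparison at an effect size of 0.50 ("the hypothesized effect sizes were medium") with 50 per arm gives 70.5%, and it is tempting to say that the true power is 70%. That calculation ignores baseline and repeated measures, so it does not reproduce the longitudinal model. With an assumed baseline correlation of 0.60 it gives 87.8%. Second, allocation by cohort might seem to add to the problem. The block sequence is applied to each cohort's list, so cohort is roughly balanced across arms. Omitting a balanced factor does not make standard errors too small.

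**Conclusion.** The concern holds in conditional form. The design is partially nested, the stated power model names only participant-level random effects, and the Aim 1 text does not say whether therapy group is a level. The 88% and 81% most plausibly assume independent ACT outcomes. If the analysis follows that model and the ICC is above zero, standard errors for the arm comparison are too small and the stated power is too high.

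At an assumed 7 per group and ICC of 0.05 to 0.10, actual type I error is 6.8% to 8.6% with complete data and 6.2% to 7.5% with 25% missing. The stated 88% falls to 83% to 79%, and the stated 81% to 77% to 73%. With only about 7 ACT groups, small degrees of freedom would lower power somewhat further. All of these sizes rest on the assumed group size and ICC, for which the document gives no values.

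**What to change.** - State that the Aim 1 model for HADS-Anxiety and the other outcomes includes a random effect for therapy group in the ACT arm only, with UC participants treated as singletons, and a small-sample degrees-of-freedom correction such as Satterthwaite or Kenward-Roger.
- Define *groups* in the power section. Unless therapy-group clustering was already included, restate the power with an assumed group size and ICC, and show a range, for example ICC 0 to 0.10.

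The cost is wording and one identifier per ACT participant. The coordinator assigns condition and schedules the groups, so membership should already be on file. The downside is slightly wider intervals and a lower stated power.
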